### {8 & 13} Trial design and timeline

After enrollment and screening assessment, 100 PD subjects will be randomly assigned (parallel assignment) in a 1:1:1:1 ratio to TIMP-RHY (25 people), or OT (25 people), or TIMP-NR (25 people) groups, or to wait for 5 weeks (Waitlist control group; 25 people). All PD subjects will undergo a magnetoencephalography (MEG) scan and a battery of tests before and after the TIMP-NR, TIMP-RHY, OT intervention, or twice separated by a 5-week period free of intervention (waitlist control group). First, to capture neural network and neurophysiological changes, participants will perform an MEG scan which engages them in an auditory-motor task. Then, clinical measures will be based on standardized PD neurologic assessments via the Unified Parkinson’s Disease Rating Scale [1], and fine motor assessments will include the Grooved Pegboard Test and finger-thumb opposition tests. Last, to capture changes in quality of life (QOL), we have included the 39-Item Parkinson's Disease Questionnaire (PDQ-39) [22]. The total duration of participation is 5–7 weeks (see the study flowchart in Fig. 1).

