### {14, 20a-c} Statistical methods and sample size

To address our primary mechanistic question, group comparison of mean Granger spectra changes using a linear mixed model controlling for sex and age will be analyzed during cued rhythmic tapping between regions of interest (ROIs: auditory, motor, precuneus, supramarginal gyrus and others) and corrected for multiple comparisons using the FDR method on the overall set of comparisons, *q* < 0.1. Statistically significant changes in Granger causality between ROIs are expected in the TIMP-RHY group but not in the OT or TIMP-NR groups due to the reliance on other motor networks, specifically those affected by PD pathology during fine motor training. A sample size per group of 25 subjects will allow us to determine between group differences with an effect size of 0.8 standard deviations/mean with 80% power and 0.05 significance, which is comparable to other studies examining neurophysiologic mechanisms of therapeutic interventions [31, 32] including similar studies using Granger causality as main outcomes in PD [33, 34]. We will perform exploratory analyses using linear regression to determine if any particular Granger feature is (1) associated with sex, age, or disease duration or severity and (2) more or less prone to motor function benefits. Based on our hypothesis, we predict fine motor training during TIMP-RHY, TIMP-NR, and OT will increase cortical motor beta and normalize gamma oscillations during the auditory-motor task in the MEG, although changes are expected to be stronger in the TIMP-RHY than in the OT and TIMP-NR groups. A 3 × 2 (group by frequency) mixed model ANOVA will be assessed to test this prediction.

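### The 3 × 2 ANOVA of beta and gamma power leaves out the waitlist arm, so it can rank the therapies but cannot test any of them against no therapy

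*Protocol article*

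**What the plan says.** The trial design section ({8 & 13}) sets up four arms: "100 PD subjects will be randomly assigned (parallel assignment) in a 1:1:1:1 ratio to TIMP-RHY (25 people), or OT (25 people"), TIMP-NR (25 people), "or to wait for 5 weeks (Waitlist control group; 25 people"). Every arm has MEG twice. The therapy arms are scanned before and after treatment, and the remaining participants "or twice separated by a 5-week period free of intervention (waitlist control group").

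The statistical section ({14, 20a-c}) makes a prediction in two parts. The first is that training has an effect: "we predict fine motor training during TIMP-RHY, TIMP-NR, and OT will increase cortical motor beta and normalize gamma oscillations". The second ranks the arms: "although changes are expected to be stronger in the TIMP-RHY than in the OT and TIMP-NR groups". One analysis is assigned to the whole prediction: "A 3 × 2 (group by frequency) mixed model ANOVA will be assessed to test this prediction". The two frequency levels are beta and gamma. The three groups are not listed, but the sentence before names exactly the three therapies, and that paragraph does not mention the waitlist.

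For the Grooved Pegboard, the same section makes the no-therapy condition the comparator and says what is expected in the waitlist group.

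**The concern.** The first part of the prediction is a claim that therapy changes oscillatory power. In a randomised trial, that claim is supported by comparison with the untreated arm. A model containing only the three therapies compares them with each other, so an effect that they share is invisible to its group and group-by-frequency tests.

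What remains is the average change from first to second scan. That change mixes the effect of therapy with repeat scanning, practice on the tapping task and five weeks of elapsed time. A statement that fine motor training raises beta or normalises gamma would then rest on uncontrolled before-after change, although a randomised control arm was scanned on the same schedule. This is not a detail left to a fuller analysis plan: the protocol names a specific model, and that model does not fit its own prediction and design.

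**Working it through.** **Inputs from the protocol.** Four arms of 25; a three-level group factor; "between group differences with an effect size of 0.8 standard deviations/mean with 80% power and 0.05 significance".

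**Assumptions not in the protocol.** Two-sided tests; outcome analysed as pre-post change with SD 1 in each band; beta-gamma correlation 0.5 where both bands enter; no dropout.

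**1. The plan's own sample size.** Normal approximation: n = 2 × ((1.960 + 0.842)/0.8)² = 24.5, so 25 per group, with power 80.7%. The exact t-test gives 79.1%. The stated figure reproduces for one comparison of two arms.

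**2. Equal therapy effects (0.8 SD in each therapy, 0 on waitlist), one band.**
- Three therapies only: the group means are identical, the noncentrality is 0, and rejection equals alpha, 5%.
- Four arms: the grand mean is 0.6, so λ = 25 × (3 × 0.2² + 0.6²) = 25 × 0.48 = 12. F(3, 96) has power 82%.
- Pooled therapies versus waitlist: SE = √(1/75 + 1/25) = 0.231; noncentrality 0.8/0.231 = 3.46; power 93%.

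**3. The same scenario in the mixed ANOVA (20,000 simulated trials).**
- Both bands moving +0.8 SD in every therapy: the group effect rejects about 5% in the 3 × 2 model and 92% in the 4 × 2 model.
- Beta +0.8 and gamma −0.8 in every therapy: the interaction rejects about 5% in the 3 × 2 model and about 100% in the 4 × 2 model.

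**4. Can the average change in the 3 × 2 model stand in for the control?** Suppose every arm drifts 0.4 SD in both bands and no therapy works. The two-band mean has SD √((1 + 0.5)/2) = 0.866. Over 75 participants its SE is 0.866/√75 = 0.10, and the noncentrality is 0.4/0.10 = 4.0. The test of average change rejects in about 98% of simulated trials. The group test of a 4 × 2 model rejects about 5%, as it should.

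**5. What the three-group model can do.** If TIMP-RHY exceeds the other two by 0.8 SD, the grand mean is 0.267 and λ = 25 × (0.533² + 2 × 0.267²) = 10.67. F(2, 72) has power 82%.

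**6. Single-therapy contrasts against waitlist** (25 versus 25, error variance from the four-arm model, 96 df): SE = √(2/25) = 0.283; noncentrality 0.8/0.283 = 2.83.

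| Two-sided alpha | Power |
|---|---|
| 0.05 (uncorrected) | about 80% |
| 0.025 (two bands) | about 71% |
| 0.005 (five contrasts × two bands = ten tests) | about 49% |

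**The case against.** **The model does test part of the prediction.** This stands. The ranking of TIMP-RHY against TIMP-NR and OT is a three-group question, with 82% power at a gap of 0.8 SD. A reader might infer that the ANOVA cannot test the prediction at all. The document does not support that; what is missing is the comparison with no therapy.

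**Equal effects are not what the protocol predicts.** Also true. The 5% figure shows a blind spot, not the expected performance. But if the therapies differ, the three-group test still speaks only to the difference between them.

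**The frequency factor.** A reader might go further and argue that, because the plan expects therapy to raise beta and normalise gamma, opposite movements would cancel in the group effect. That argument fails. The ANOVA also tests the interaction, which is what responds to opposite movement: with TIMP-RHY alone moving +0.8 SD in beta and −0.8 SD in gamma, the 3 × 2 interaction rejects in about 100% of simulated trials. The protocol also gives no direction for gamma.

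**The waitlist is used elsewhere.** It is the comparator for the Grooved Pegboard question, and the Granger group comparison, which is the test named for the primary mechanistic question, is not restricted to three groups. It would be wrong to infer that the arm is unused in the trial.

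**The omission is inferred.** The groups are not listed. Still, a three-level factor in a four-arm trial, directly after a sentence naming the three therapies, leaves no other plausible reading.

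**Conclusion.** The point holds for the comparison with no therapy. As stated, the beta/gamma ANOVA leaves out the randomised control and so cannot test whether any therapy changes either band relative to no therapy. With equal therapy effects its group and interaction tests reject at 5%. Once the waitlist is included, the same data give 82% power with a one-way four-group F-test and 93% with the pooled contrast.

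These figures rest on a 0.8 SD effect in every therapy, none on waitlist, 25 complete pairs per arm and analysis of change scores. They illustrate the gap and do not forecast the trial's result. The 93% belongs to the pooled contrast only and should not be read as the power for each therapy separately. The sample size is not called into question by this point.

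**What to change.** Replace the 3 × 2 model with a 4 × 2 (group by frequency) model on pre-post change that includes the waitlist, and name the four groups. State planned contrasts, reported by band:

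1. pooled therapies versus waitlist, tested first;
2. each therapy versus waitlist;
3. TIMP-RHY versus TIMP-NR and versus OT.

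State how multiplicity is controlled across contrasts and bands, and base any claim that therapy changes beta or gamma on items 1 and 2.

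The cost is a change of wording and more contrasts. Correction is not free: power for a single-therapy contrast falls from about 80% to about 71% at alpha 0.025, or about 49% under Bonferroni over ten tests. Testing the pooled contrast first limits that loss for the main question. No added participants, visits or scans are needed, because the waitlist scans are already in the design. Whether they have been completed cannot be told from the article, whose trial status section only gives the end of 2023 as the expected date of the last assessments.

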### {12} Outcomes

Primary mechanistic outcome for this study will be neurophysiology. We aim to uncover the underlying pathways utilized by NMT in the PD brain. Neurophysiologic data will be collected via MEG before and after any therapy or twice separated by a five week interval. We will be using a whole head neuromagnetometer (4D Neuroimaging) with an array of 248 sensors at a 678.17 Hz sampling rate and an acquisition bandwidth of 0.1–200 Hz during an auditory-motor task. Participants will be presented with 6 sequences of 30 ms acoustic burst stimuli (2000 Hz, intensity of 70 dB above subjective threshold) presented at 1 Hz. Each sequence will last 30 s with a 5-s break (180 total stimuli). They will be asked to tap their dominant index finger with the stimuli. After MEG data cleaning and preprocessing, time-frequency transformation and source localization will allow to measure relative beta and gamma oscillatory power in our regions of interest. We will evaluate group changes in directional functional connectivity between auditory, motor, and other regions of interest in the frequency domain using Granger causality.

Our primary motor outcome for this study will be finger dexterity. Similarly to our mechanistic outcome, will record changes in the total score on the Grooved Pegboard Test (GPT), which is a manipulative dexterity test consisting of 25 holes with randomly positioned slots [24] commonly used as a test of fine motor performance [25]. As the pegs must be rotated into position to be successfully placed, the GPT adds a dimension of complexity not found in other motor tasks and thus has been found to be a sensitive instrument in detecting general slowing due to medication or disease progression. In PD, the Grooved Pegboard Test has also been used extensively for identifying lateralized impairment [26] and as a motor outcome of clinical trials [27]. The time taken to complete the GPT with each hand is the score to be used in this application. Reliability for the test is good. Secondary motor outcomes designated for this study also assess fine motor abilities and will include the score on the finger-thumb opposition assessment (derived from the Neurological Evaluation Scale [28];) and the score from the finger tapping test on the UPDRS part III.

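### The 3 × 2 ANOVA for beta and gamma leaves out the waitlist arm, so it cannot test whether training itself changes these rhythms

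*Protocol article*

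**What the plan says.** Section {8 & 13} (Trial design and timeline) describes four arms, "randomly assigned (parallel assignment) in a 1:1:1:1 ratio to TIMP-RHY (25 people") and likewise 25 each to OT and TIMP-NR, "or to wait for 5 weeks (Waitlist control group; 25 people"). Every arm has MEG and the test battery twice: before and after therapy, "or twice separated by a 5-week period free of intervention (waitlist control group"). Section {12} (Outcomes) repeats the schedule: "Neurophysiologic data will be collected via MEG before and after any therapy or twice separated by a five week interval". It describes relative beta and gamma power under the primary mechanistic outcome.

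Section {14, 20a-c} (Statistical methods and sample size) makes a prediction in two parts:

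- **Absolute part:** "we predict fine motor training during TIMP-RHY, TIMP-NR, and OT will increase cortical motor beta and normalize gamma oscillations during the auditory-motor task".
- **Relative part:** "although changes are expected to be stronger in the TIMP-RHY than in the OT and TIMP-NR groups".

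The test for both is a 3 × 2 design ("group by frequency) mixed model ANOVA will be assessed to test this prediction"). The two frequencies are beta and gamma, and the sentence before names three therapies. The waitlist is not mentioned anywhere in the mechanistic part of the section. In the clinical part of the same section, the Grooved Pegboard (GPT) question is set against the condition without therapy, and an expectation for the waitlist arm is stated for both GPT and quality of life.

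**The concern.** A model whose group factor has only the three therapies compares therapies with each other. It can show that one changes beta or gamma more than another, but not that therapy changes them compared with no therapy. The second statement is the absolute part of the prediction, and the article assigns it to this model.

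Without the waitlist, the absolute part could be judged only from the shift between the first and second scan in treated participants. That shift may also contain greater familiarity with the tapping task, habituation to the scanner and tones, and whatever else changes over five weeks. The waitlist scans would separate these from training. At stake is a mechanistic claim about fine motor training made without the randomised control that the trial enrols 25 people to provide.

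**Working it through.** **Inputs from the article.** Four arms of 25; two MEG scans in every arm; group factor with three levels; planning effect 0.8 SD; power 80%; significance level 0.05. Sidedness is not stated and is taken as two-sided. All calculations below treat one frequency at a time, use the SD of change as unit, and assume complete data.

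**The plan's own figure.** n per group = 2 × ((1.960 + 0.842)/0.8)² = 24.5, rounded up to 25. Power with 25 per group is 81% by the normal approximation and 79% by the noncentral t. The stated 25 per group is reproduced (a one-sided test would give 20). It is a figure for a difference between two groups; none is given for the 3 × 2 ANOVA.

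**What the group test can see.** The noncentrality of the F-test is λ = n Σ(mean of arm − overall mean)², with n = 25.

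| True mean change (SD) | Model | λ | Rejection rate |
|---|---|---|---|
| Three therapies 0.8 each | three groups | 0 | 5% |
| Three therapies 0.8 each, waitlist 0 | four groups | 25 × 0.48 = 12.0 | 82% |
| TIMP-RHY 0.8, other two therapies 0 | three groups | 25 × 0.427 = 10.7 | 82% |
| TIMP-RHY 0.8, other three arms 0 | four groups | 12.0 | 82% |

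The first two rows are the absolute part: an equal benefit from all therapies is invisible to the three-group test. The last two rows are the relative part, which is equally well served by either model.

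**What a pre-post reading would risk.** The documents give no retest drift, so a range is assumed: the same drift in all four arms and no therapy effect. For a one-sample t-test on change, the noncentrality is drift × √n, with n = 75 pooled or 25 in one arm. At 0.3 SD pooled, for example, it is 0.3 × √75 = 2.60 against a critical value of 1.99, which gives 73%.

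| Assumed drift (SD of change) | Falsely significant, pooled 75 | Falsely significant, one arm of 25 | Therapy versus waitlist |
|---|---|---|---|
| 0.1 | 14% | 8% | 5% |
| 0.2 | 40% | 16% | 5% |
| 0.3 | 73% | 30% | 5% |
| 0.5 | 99% | 67% | 5% |

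**Power of the contrast with the waitlist.** For 75 versus 25 the noncentrality is d/√(1/75 + 1/25). At d = 0.8 it is 3.46, giving 93% power; at d = 0.65 it is 2.81, giving 80%.

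**Effect of a fourth arm on the therapy contrasts.** For TIMP-RHY versus one other therapy at 0.8 SD, the noncentrality is 0.8/√(2/25) = 2.83. Error degrees of freedom are 3 × 24 = 72 or 4 × 24 = 96.

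| Rule | Three arms | Four arms |
|---|---|---|
| Unadjusted prespecified contrast | critical t 1.99, power 79.7% | critical t 1.98, power 80.0% |
| All pairs, Tukey | critical t 2.39, power about 67% | critical t 2.61, power about 59% |

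Prespecified contrasts therefore lose nothing, but all-pairs comparison over four arms would.

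**The case against.** The strongest reply is that the specific aim survives. Section {6b & 7} (Research objectives and comparators) asks whether adding external rhythmic cueing mobilises different networks. That is TIMP-RHY against TIMP-NR, with OT as clinical comparator, and the 3 × 2 model tests it by randomised comparison. This stands, and limits the point to the absolute part of the prediction.

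It is also fair to say that the article writes no pre-post test. The ANOVA has no time factor, and the response is not stated to be change or post-treatment value. A reader might infer that the trial plans an uncontrolled pre-post test with a 73% or 99% false-positive rate. The documents do not support that. The rates belong to a test that is not in the plan and to assumed drifts; at 0.1 SD they are 14% pooled and 8% per arm. What the text does show is that the stated model cannot answer the absolute question.

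A reader might also infer that the waitlist MEG data are collected and then never used, or that the Granger analysis has the same fault. Neither follows. The Granger linear mixed model, which the article ties to the primary mechanistic question, is called a group comparison with no number of groups given. The exploratory regression of motor performance on beta change does not exclude the waitlist either.

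A separate analysis plan might contain a four-arm model. But 3 × 2 is an explicit specification in the article, not a detail left open.

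**Conclusion.** The point holds for this one ANOVA. The model assigned to the prediction that training changes beta and gamma omits the only arm that could show it, although that arm is randomised and scheduled for two scans. The same section uses the comparison without therapy for GPT. The between-therapy part is unaffected.

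The 5% rejection rate under equal benefit follows from the model alone and needs no assumption about drift. How misleading a pre-post reading would be depends on a drift that the documents do not give. The power figures assume no dropout, while the article analyses complete pre-post pairs only.

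This should be fixed. It is not a fatal flaw: the primary mechanistic question is tied to the Granger model, the randomised comparison between therapies is intact, and the remedy is small.

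**What to change.** - Replace the 3 × 2 model with a four-arm (4 × 2) analysis of post-minus-pre change in beta and gamma: TIMP-RHY, TIMP-NR, OT and waitlist.
- Prespecify a therapy-minus-waitlist contrast for the absolute part, and claim that training changes beta or gamma only from that contrast.
- Keep TIMP-RHY versus TIMP-NR and TIMP-RHY versus OT as prespecified contrasts for the relative part, rather than all-pairs Tukey comparisons over four arms.

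The cost is wording only. The waitlist scans are already scheduled, so no participants or visits are added.

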We will address our clinical research question by determining whether there is a significant change in fine motor skills following TIMP-RHY, TIMP-NR, and OT due to fine motor training compared to the non-therapy condition. We predict that TIMP-RHY will decrease mean GPT scores to a higher extent than the TIMP-NR and the OT groups. We will use an ANOVA F-test model to test this prediction on the mean GPT score change as well as pairwise contrasts with Tukey-Kramer correction for multiple comparisons to assess where the differences are. We do not expect such changes in the waitlist group due to the absence of fine motor strengthening. Given the large effect size of 0.8 sd/mean seen in other PD studies using the GPT grooved pegboard test as main outcome [35, 36], we anticipate that our sample size of 25 per group will allow us to determine a group difference of 15% decreased time using the dominant hand and to be comparable to published data [37]. We will also perform exploratory analyses using regression modeling to assess whether (1) sex, age, or disease severity and (2) cortical motor beta power changes are correlated with fine motor tests performance.

We will address our QOL research question by assessing changes in the PDQ-39 and CGI-I scales. As fine motor skills may improve, we expect a decrease in mean total scores (the higher the scores the higher the problems with quality of life, depression/anxiety and how things have changed) after a 5-week TIMP-RHY session and to a lower extent after OT or TIMP-NR sessions. We do not expect a change of QOL mean scores in the waitlist group.

Only complete sets of data (including both pre and post) will be included in the analysis. No imputation or other methods for handling missing data will be used during the analysis process.

No interim or subgroup analyses will be performed.

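### The omnibus F-test named for the pegboard prediction cannot show that TIMP-RHY beats TIMP-NR and OT; the two contrasts that can are only follow-up and carry a six-way correction

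*Protocol article*

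**What the plan says.** The section on statistical methods and sample size ({14, 20a-c}) puts two questions to the pegboard, the primary motor outcome named under {12} Outcomes.

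- The first is "whether there is a significant change in fine motor skills following TIMP-RHY, TIMP-NR, and OT due to fine motor training compared to the non-therapy condition".
- The second is directional and concerns two particular pairs: "We predict that TIMP-RHY will decrease mean GPT scores to a higher extent than the TIMP-NR and the OT groups".

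The test follows directly: "We will use an ANOVA F-test model to test this prediction on the mean GPT score change". The same sentence goes on "as well as pairwise contrasts with Tukey-Kramer correction for multiple comparisons to assess where the differences are". On the waitlist the section says: "We do not expect such changes in the waitlist group due to the absence of fine motor strengthening".

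The groups entering the ANOVA are not listed. The text does not say which contrasts must succeed for the prediction to be upheld.

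**The concern.** An omnibus F-test has no direction and responds to any difference among the arms. The protocol already expects therapy to differ from waitlist, so a four-arm F-test is likely to be significant whether or not rhythm adds anything. It therefore cannot decide between the prediction and its negation, although the wording ties it to the prediction.

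The contrasts that can decide are described as a way to find where differences lie, and all six pairs stand on an equal footing. That has two consequences:

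- A mixed result, such as TIMP-RHY ahead of one comparator only, has no clear reading.
- The correction is paid for pairs that the prediction does not involve, such as TIMP-NR versus OT.

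What rhythmic cueing adds is the central contrast of the trial ({6b & 7} Research objectives), so the test that settles it should be the one with the right target and the best valid power.

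**Working it through.** **Inputs.** From the protocol: 25 per arm in four arms; effect size 0.8, written as SD/mean and read here as 0.8 SD; 80% power; significance level 0.05. Assumptions: two-sided tests, a common SD of 1, all 25 per arm complete, and the waitlist included in the ANOVA. Effects are reductions in pegboard time, so larger is better.

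**1. The protocol's own figure.** "A sample size per group of 25 subjects will allow us to determine between group differences with an effect size of 0.8 standard deviations/mean". The power claimed for this is 80%. For an unadjusted two-group comparison, the non-centrality is 0.8 × √(25/2) = 2.83. Power is 80.7% by the normal approximation and 79.1% by the t-test. The figure reproduces, but for one unadjusted pair.

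**2. The F-test when the prediction is false.** Take true benefits of 0.8, 0.8, 0.8 and 0 (waitlist). The mean is 0.6, the squared deviations sum to 3 × 0.04 + 0.36 = 0.48, and λ = 25 × 0.48 = 12. With 3 and 96 df, P(F significant) = 0.824. The value depends on the common benefit over waitlist:

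| Benefit (SD) | 0.4 | 0.5 | 0.6 | 0.7 | 0.8 | 0.9 | 1.0 |
|---|---|---|---|---|---|---|---|
| P(F significant) | 0.26 | 0.40 | 0.55 | 0.70 | 0.82 | 0.91 | 0.96 |

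At 0.8 SD it is 0.76 with 22 completers per arm and 0.72 with 20. If the waitlist were left out of the ANOVA it would be the nominal 0.05.

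**3. The planned contrasts in the same situation.** For four groups and 96 df the studentized range critical value is 3.698, so the Tukey critical |t| is 3.698/√2 = 2.615. In simulated trials with benefits 0.8, 0.8, 0.8 and 0, TIMP-RHY is declared better than at least one other therapy in about 1.0%, and better than both in about 0.05%.

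**4. Power of the planned contrasts.** One 0.8 SD pair at the Tukey threshold has power 0.59. If TIMP-RHY truly beats both by 0.8 SD (benefits 1.6, 0.8, 0.8, 0), both contrasts are significant with probability about 0.43, and exactly one in about 32% of trials.

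**5. Both contrasts required, each at two-sided 0.05.** The critical |t| with 96 df is 1.985. The claim is that TIMP-RHY beats both, so it is false whenever at least one difference is zero or negative. The chance that this contrast is significant in favour of TIMP-RHY is then at most 2.5%, whatever the other does. This is the intersection-union argument.

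| Situation | Both at Tukey threshold | Both at two-sided 0.05 |
|---|---|---|
| Three therapies equal, prediction false | about 0.05% | about 0.5% |
| Worst case, prediction false | below 2.5% | at most 2.5% |
| TIMP-RHY better than each by 0.8 SD | about 0.43 | about 0.69 |

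**The case against.** The strongest reply is that the sentence must be read whole. The verb governs both the F-test and the pairwise contrasts, and TIMP-RHY versus TIMP-NR and versus OT are among those contrasts. An F-test followed by contrasts is a standard sequence. This stands: the prediction is tested directly somewhere in the plan.

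A reader might infer from the 82% that the plan would falsely declare TIMP-RHY superior in most trials. The documents do not support that, because the contrasts they specify hold such a finding to about 1% in the same situation. For the claim of beating both, the Tukey rule is stricter than the rule proposed here (0.05% against 0.5%).

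It is also fair that the ANOVA groups are not listed, and that the parallel MEG prediction uses a three-group model. Four groups is the likelier reading here, because the clinical question is put "following TIMP-RHY, TIMP-NR, and OT due to fine motor training compared to the non-therapy condition", but it is not certain.

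Two further replies carry less weight. All-pairs Tukey-Kramer is defensible when every pair matters, but the prediction concerns two pairs only. A detailed decision rule may sit in an analysis plan that is not shown, and its absence is not the point. The point is that the article does name a test for the prediction, and that test answers a different question.

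**Conclusion.** The point holds as a mismatch between a stated prediction and the test named for it, together with an avoidable loss of power. It does not hold as a claim that the plan's inference is invalid: the Tukey-Kramer contrasts are valid and address the right pairs.

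A significant F says little about TIMP-RHY against the other therapies. The 82% measures only that, and it rests on a 0.8 SD benefit over waitlist, 25 completers per arm and a four-arm ANOVA. The loss of power, from about 0.69 to about 0.43, rests on a true advantage of 0.8 SD over each comparator and the same 25 completers. That advantage is the protocol's own effect size: "Given the large effect size of 0.8 sd/mean seen in other PD studies using the GPT grooved pegboard test as main outcome". The conclusion that F cannot confirm the prediction does not depend on these values if the waitlist is included. A three-group F would also be non-directional and would not require TIMP-RHY to beat both.

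**What to change.** In section {14, 20a-c}:

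1. State that the prediction is judged on TIMP-RHY versus TIMP-NR and TIMP-RHY versus OT, and is supported only if both favour TIMP-RHY at two-sided 0.05. No correction between the two is needed.
2. State that the F-test is not used to confirm the prediction. Report it, and TIMP-NR versus OT, as supportive.
3. Keep the three therapy-versus-waitlist comparisons as the separate first clinical question, with their own multiplicity correction. A preliminary TIMP-RHY-versus-waitlist test is not needed, since it is no part of the prediction.
4. List the groups in the ANOVA.

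The cost is a change of wording, with the same model and data. TIMP-RHY beating only one comparator would not count as support. The false-claim rate for beating both rises from about 0.05% to about 0.5% when the three therapies are equal, still within the 2.5% bound. The two clinical questions are each controlled separately, not jointly, and the text should say so.

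### The primary motor comparison uses an unadjusted pegboard change score although every analysed participant has a baseline time; a baseline-adjusted model would usually be more efficient, by an amount that depends on an unstated correlation

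*Protocol article*

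**What the plan says.** All references are to the protocol article.

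- **Outcome.** Section {12} states: "Our primary motor outcome for this study will be finger dexterity". It is measured as time to complete the GPT.
- **Motor model.** Section {14, 20a-c} says: "We will use an ANOVA F-test model to test this prediction on the mean GPT score change". Group differences are then located by "pairwise contrasts with Tukey-Kramer correction for multiple comparisons to assess where the differences are". No covariate is named.
- **Age and sex in the motor analysis.** They appear only in a secondary role: "We will also perform exploratory analyses using regression modeling to assess whether (1) sex, age, or disease severity".
- **Mechanistic model.** The same section does name covariates for the other primary outcome: "group comparison of mean Granger spectra changes using a linear mixed model controlling for sex and age".
- **Baseline data.** Section {8 & 13} says: "All PD subjects will undergo a magnetoencephalography (MEG) scan and a battery of tests before and after". The waitlist group is also tested twice. Because only participants with both assessments are analysed, everyone in the analysis has a baseline GPT time.
- **Randomisation.** Sections {16a-c} describe a list of random numbers made in a spreadsheet and mention no stratification factor.
- **Sample size.** The basis is given as: "A sample size per group of 25 subjects will allow us to determine between group differences with an effect size of 0.8 standard deviations/mean". The power claimed for this is 80%, at a significance level of 0.05. The GPT paragraph uses the same 0.8 and the same 25 per group.

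**The concern.** A change score subtracts the whole baseline value, which is the best correction only when the regression of post on baseline has slope 1. With equal variances at the two visits that slope is r, which is below 1. The change score therefore over-corrects: a group that starts slower by chance will on average appear to improve more. With 25 per group and no stratification described, such imbalances are to be expected.

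ANCOVA on baseline estimates the slope from the data. It removes the part of the contrast that is due to the observed imbalance and reduces the error variance. The article names a model for this outcome and names covariates for the other primary outcome, so the unadjusted form is a stated choice and not a detail lost in condensing. At stake are the precision of the four-group comparison and how far a single result can be moved by chance differences at baseline.

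**Working it through.** **Inputs.** From the article: four groups of 25, effect 0.8, 80% power, alpha 0.05, Tukey-Kramer contrasts. Assumed: 0.8 is in SDs of the change score; pre and post variances are equal (s²); there is a common slope; alpha is two-sided. The pre-post correlation r is not given. The article says only that the test's reliability is good, so r is varied from 0.5 to 0.95.

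**1. The plan's own figure.** n per group = 2(1.960 + 0.842)²/0.8² = 24.5, so 25. This matches. Power at 25 per group is 80.7% (normal approximation), 79.1% (two-sample t, 48 df) or 80.0% (pooled error, 96 df), without correction for multiple contrasts.

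**2. The planned contrast.** The noncentrality is 0.8 × √(25/2) = 2.83. The Tukey critical value for four groups and 96 df, on the t scale, is 2.615. Pairwise power is 58.6%. This is the reference for the adjusted model.

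**3. Variance ratio.**
- Change score: 2s²(1 − r).
- ANCOVA: s²(1 − r²).
- Ratio: (1 + r)/2.

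The effective standardised effect is 0.8/√[(1 + r)/2 × k]. Here k allows for chance covariate imbalance: k = 1 + 1/94 with baseline only (95 df), and k = 1 + 3/92 with baseline, age and sex (93 df).

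**4. Power at 25 per group.** The last column assumes that age and sex explain nothing further.

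| r | Variance ratio | Uncorrected, baseline only | Tukey, baseline only | Tukey, baseline + age + sex |
|---|---|---|---|---|
| Change score | 1 | 80.0% | 58.6% | – |
| 0.5 | 0.75 | 89.5% | 73.5% | 72.4% |
| 0.7 | 0.85 | 85.6% | 66.8% | 65.6% |
| 0.8 | 0.90 | 83.5% | 63.7% | 62.5% |
| 0.9 | 0.95 | 81.5% | 60.8% | 59.6% |
| 0.95 | 0.975 | 80.5% | 59.4% | 58.2% |

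If age and sex explained 5% of the remaining variance, the last column would be 75.1, 68.4, 65.3, 62.4 and 61.0%.

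**5. Simulation check** (6,000 runs, four groups of 25, uncorrected contrast, baseline only). Power went from 79.7% to 88.8% at r = 0.5, from 80.1% to 86.1% at 0.7, and from 79.7% to 81.4% at 0.9. Type I error stayed near 5% for all models (4.8 to 5.8%; 4,000 null runs each).

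**6. Exposure to imbalance.** The standard error of a baseline difference between two groups is √(2/25) = 0.28 SD. A one-standard-error imbalance moves the change-score contrast by 0.28 × (1 − r) in raw SDs, which is 0.28 × √[(1 − r)/2] in SDs of change. That is 0.14 at r = 0.5, 0.11 at 0.7 and 0.06 at 0.9, or about 18%, 14% and 8% of the 0.8 target.

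**7. The other reading of 0.8.** If it is in SDs of the raw score, uncorrected power still favours ANCOVA: 80.0% to 89.5% at r = 0.5, and 95.1% to 97.4% at r = 0.7.

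**The case against.** The strongest reply is that nothing here is an error. ANOVA on change is unbiased over randomisation and holds its type I error, and the stated 25 per group reproduces. That stands. A reader might infer that the planned test is biased or invalid. The documents do not support this: the imbalance effect is conditional on the allocation that happens to occur, and it averages to zero.

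A second reply is that the gain may be small. A test described as reliable and repeated after five weeks may have a high r. At r = 0.9 the Tukey gain is about 2 points with baseline only and 1 point with uninformative age and sex; near 0.95 the latter model gains nothing. This stands too. Saying that adjustment for baseline, age and sex always buys power at no cost goes too far: nearly all the gain comes from baseline GPT.

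Three further inferences should be resisted:

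- **Shortfall below 80%.** The 58.6% arises because the sample size ignores the Tukey correction, not because baseline is left out. It is a separate matter.
- **The Granger model.** The article does not list baseline Granger values as a covariate, but it gives only an outline of that mixed model, and the GPT calculation does not carry over to it.
- **Log time.** The target of a 15% shorter time does not require analysis on the log scale, which would change the quantity estimated.

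**Conclusion.** The point holds as a recommendation on efficiency and robustness. The article fixes an unadjusted change-score analysis for its primary motor outcome while holding a baseline value for every participant analysed. With baseline adjustment, Tukey pairwise power would rise from 58.6% by about 15 points at r = 0.5, 8 at 0.7, 5 at 0.8, 2 at 0.9 and 1 at 0.95. Adding age and sex lowers these by about 1 point if they explain nothing. Over this range the adjusted contrasts remain below 80%.

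The direction is secure unless r is very close to 1. The size is not, because it rests on an r that the article does not give, as well as on equal variances, a common slope and 0.8 being in SDs of change.

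**What to change.** Before unblinding, prespecify the primary motor analysis as an ANCOVA of post-intervention GPT time on group and baseline GPT time (same hand), with Tukey-Kramer comparisons of the adjusted means. Age and sex may be added so that the two primary models agree, but not in the expectation of much power. The existing exploratory regressions can stay; they do not replace this adjustment.

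No extra participants, visits or measurements are needed. The statistical cost is 1 error degree of freedom of 96 with baseline only, or 3 with age and sex. The procedural cost is real: recruitment began in February 2019 and the analysis is published, so this is a protocol amendment. It goes to the review board and, if treated as an important modification, to the sponsor, and its date relative to unblinding should be recorded.
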